## Abstract

**Background:**

Hypertension is a major risk factor for cardiovascular disease and is responsible for 14% of all annual deaths globally. The prevalence of hypertension varies across occupational groups, possibly affected by differences in the working environment. One work-related factor that might impose a risk for hypertension is lifting due to the acute large increases in blood pressure (BP) during lifting.

**Objective:**

The aim of this study is to explore associations between heavy occupational lifting and hypertension in the Copenhagen City Heart Study.

**Methods:**

This study will use data from the third, fourth, and fifth examination of the Copenhagen City Heart Study. The dataset contains person-based information on health as well as a large variety of biological, environmental, and lifestyle-related factors. Using a cross-sectional design, we will investigate the association between heavy occupational lifting and hypertension, defined as using antihypertensive drugs or having a measured systolic BP (SBP) ≥140 mm Hg or diastolic BP (DBP) ≥90 mm Hg. Furthermore, in a prospective design, we will investigate the association between heavy occupational lifting and risk of becoming an SBP case, defined as the shift from not using antihypertensive drugs in examination n to use of antihypertensive drugs in examination n+1 or an above median delta value of SBP (SBP in examination n+1−SBP in examination n).

**Results:**

In the third examination in 1991-1994, 10,135 out of 16,560 participants attended (61.20%), in the fourth examination in 2001-2003, 6237 out of 12,599 participants attended (49.50%), and in the fifth examination in 2011-2015, 4550 out of 9765 participants attended (46.59%). On the basis of the inclusion criteria of answering to the level of occupational physical activity, 5031 observations were excluded from examination 3, 2600 from examination 4, and 1621 from examination 5. Hence, the final populations for the cross-sectional and prospective analysis are assumed to include less than 7166 participants in the cross-sectional analysis and less than 1850 participants in the prospective analysis due to the additional inclusion criteria of measured BP and use of antihypertensive drugs.

**Conclusions:**

One-third of the workforce in Europe reports to carry or move heavy loads regularly during working hours (6th survey in Eurofound). Thus, if this study shows occupational lifting to increase the risk for hypertension, the prevention for hypertension can be improved.

## Introduction

### Background

Hypertension is a major risk factor for cardiovascular diseases [1,2] and is responsible for 14% of all annual deaths globally [1]. The prevalence of hypertension varies across occupational groups, possibly affected by differences in the working environment. One work-related factor that might impose a risk for hypertension is lifting [3,4]. Heavy lifting causes acute large increases in blood pressure (BP) [5]. These increases in BP during heavy lifting are explained by the constriction of the vessels due to contraction of muscle fibers surrounding the vessels as well as the pressor reflex, both leading to an increased peripheral resistance and thereby also an increased BP [5]. Thus, because some workers perform occupational lifting for several hours per day, many days per week, higher BP or hypertension is likely to occur [6]. Yet, scientific knowledge of the relation between heavy occupational lifting and hypertension is limited. Previous studies investigating this relation have found occupational lifting to increase risks for myocardial infarction [3] and ischemic heart disease [4] in population studies including both sexes and workers from white- and blue-collar occupations. However, one study, only including males from blue-collar occupations did not find increased risk for ischemic heart disease from occupational lifting [7]. As the study by Petersen and colleagues [4] found the risks from lifting to be most pronounced among workers with low occupational physical activity (OPA) but high exposure to lifting, it seems that investigations of associations between occupational lifting and risk for hypertension benefit from populations including both sexes and a variety of occupations.

Conversely, heavy lifting might also impose beneficial effects on BP, since resistance training involving heavy lifting has been shown to reduce resting BP [8,9]. Additionally, it is also unknown whether effects of exposure to heavy occupational lifting differ between participants with and without preexisting hypertension. A Danish survey from 2016 [10] concludes that 22% of the Danish workforce are exposed to occupational lifting during ≥25% of their working hours. Likewise, 32% of European workers report to carry or move heavy loads regularly during working hours (6th survey in Eurofound). Thus, an investigation of the association between occupational lifting and risk of hypertension in population studies including both sexes and both blue- and white-collar occupations, might uncover a potential for prevention of cardiovascular diseases for a quite large proportion of the working population.

### Objective

The aim of this study is to explore associations between heavy occupational lifting and hypertension in the Copenhagen City Heart Study. Associations will be investigated both cross-sectionally and prospectively, among randomly selected citizens from two districts of Copenhagen, Denmark.

For the cross-sectional analysis, the primary null-hypothesis is that there is no association between heavy occupational lifting and hypertension. For the prospective analysis, the primary null-hypothesis is that there is no association between heavy occupational lifting at baseline and increased resting systolic BP (SBP) 10 years later.

## Methods

### Overview

This study will use data from the Copenhagen City Heart Study, which have been collected via health examinations and questionnaires in five examinations, namely 1976-1978, 1981-1983, 1991-1994, 2001-2003, and 2011-2014, on random population samples from two districts of Copenhagen. The sample of the first examination consisted of approximately 20,000 people in the age range of 20 to 93 years. The samples of the other examinations consisted of all previously invited people plus a new sample of people, who were younger than 20 years at the time of the first examination. In the first examination, 73.58% responded (14,223/19,329), this dropped to 49.50% (6237/12,599) in the fourth examination [11]. The dataset contains person-based information on health, as well as a large variety of biological, environmental, and lifestyle-related factors. This study will include data from the third, fourth, and fifth examination of the Copenhagen City Heart Study for the analysis of the association between heavy occupational lifting and hypertension without inclusion of effect of time. Using a cross-sectional design, we will investigate the association between heavy occupational lifting and hypertension, defined as using antihypertensive drugs or having a measured SBP ≥140 mm Hg or DBP ≥90 mm Hg. Furthermore, in a prospective design, we will investigate the association between heavy occupational lifting and risk of becoming an SBP case across a time span of approximately 10 years. An SBP case will be defined as the shift from not using antihypertensive drugs in examination n to use of antihypertensive drugs in examination n+1 or an above median delta value of SBP (SBP in examination n+1−SBP in examination n). Analyses of associations both cross-sectional and prospectively hold the potential of evaluating associations both with and without inclusion of the effect of time.

### Inclusion Criteria

For the cross-sectional analysis, the criteria for inclusion will be participation in the BP measurement and having responded to the questions regarding level of OPA (also including heavy lifting) and antihypertensive drug usage.

Inclusion criteria for the prospective analysis will be (1) that the participant answered the question regarding level of OPA at the third examination and/or fourth examination (n); (2) that he or she was normotensive at examination n; and (3) that he or she participated in the BP measurement and gave a valid answer to the questions regarding antihypertensive drug usage in examination n and n+1.

We believe that potential effects of heavy occupational lifting on BP may be concealed, reversed, or otherwise distorted by effects from antihypertensive drugs. The reason for excluding participants with hypertension at baseline from the prospective analysis is that they either are treated with antihypertensive drugs at examination n or, due to being detected as hypertensive at the health examination, are likely to receive treatment with antihypertensive drugs in the time period between examination n and examination n+1.

### Assessment of Exposure

In all 3 examinations, the self-reported information on level of OPA was obtained by asking the question: “Please describe your level of OPA within the past year” with the following response categories: “(1) predominantly sedentary; (2) sitting or standing, some walking; (3) walking, some handling of material; (4) heavy manual work.” If answering 3 or 4, an additional question regarding heavy occupational lifting was applied. The question was: “Do you lift heavy burdens?” with the response categories: “(1) yes and (2) no.” Participants will be classified as exposed to heavy occupational lifting by answering “yes” to the question concerning heavy burdens, and those participants answering 1, 2, and 3 or 4 in combination with not lifting heavy burdens will be classified as the reference group.

Between the examinations of data collection, we do not have any information about their exposure to OPA or lifting. However, for the prospective analysis, a measure of the stability of exposure was accounted for by cross-tabulating the self-reported exposure at examination 3 by exposure at examination 4 and also the self-reported exposure at examination 4 by exposure at examination 5. Among those participants responding to the self-reported exposure to OPA at examinations 3 and 4, 13.4% (329/2459) stated to be exposed to heavy lifting in examination 3 and 12.0% (295/2459) in examination 4. Among those participants responding to the self-reported exposure to OPA at examinations 4 and 5, 8.29% (146/1762) stated to be exposed to heavy lifting in examination 4 and 6.81% (120/1762) in examination 5. An evaluation of the agreement (Cohen kappa) between exposure to heavy occupational lifting in examinations 3 and 4 was .30, and the agreement between exposure to heavy occupational lifting in examinations 4 and 5 was .40, indicating a fair agreement between exposure to heavy occupational lifting across examinations (see Tables 1-4) [12].

**Table 1 table1:** Number of participants who responded to the questions on level of occupational physical activity (OPA) at examinations 3 and 4.

Examination 3 (1991-1994)	Examination 4 (2001-2003)			
	1^a^	2	3	4
1	599	223	45	9
2	173	511	123	8
3	57	210	367	34
4	3	21	26	50

^a^1=predominantly sedentary; 2=sitting or standing, some walking; 3=walking, some handling of material; 4=heavy manual work.

**Table 2 table2:** Number of participants who reported to have heavy occupational lifting at examinations 3 and 4.

Examination 3 (1991-1994)	Examination 4 (2001-2003)		
	Yes	No
Yes	236	93
No	59	90

**Table 3 table3:** Number of participants who responded to the questions on level of occupational physical activity (OPA) at examinations 4 and 5.

Examination 4 (2001-2003)	Examination 5 (2011-2015)			
	1^a^	2	3	4
1	523	163	30	1
2	175	352	73	3
3	43	112	219	13
4	7	13	13	22

^a^1=predominantly sedentary; 2=sitting or standing, some walking; 3=walking, some handling of material; 4=heavy manual work.

**Table 4 table4:** Number of participants who reported to have heavy occupational lifting at examinations 4 and 5.

Examination 4 (2001-2003)	Examination 5 (2011-2015)	
	Yes	No
Yes	94	52
No	26	95

### Assessment of Outcome

The primary outcome in the cross-sectional analysis will be hypertensive status. Participants will be classified as hypertensives if they use antihypertensive drugs or they had a measured SBP ≥140 mm Hg or DBP ≥ 90 mm Hg.

In the prospective analysis, the primary outcome will be classified as an SBP case. The SBP case definition is the shift from no use of antihypertensive drugs in examination n to use of antihypertensive drugs in examination n+1 or an above median delta value of SBP (SBP in examination n+1−SBP in examination n).

In addition, secondary analyses will be conducted with pulse pressure (pulse pressure=SBP−DBP), mean arterial pressure (mean arterial pressure=([2 × DBP] + SBP/3) and mid BP (½ SBP + ½ DBP) as outcomes [13].

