### Criteria for Statistical Significance

The overall significance level will be set at .05. A Bonferroni correction will be applied, due to the similarity of the two proposed hypotheses, which means that each of the two primary hypotheses will be tested at a significance level of *P*=.025. Secondary analyses will be regarded as exploratory and will therefore not be tested for statistical significance, but the precision will be reported by 95% CI. They may influence the interpretation of findings of the primary analyses.

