#### Analysis on Other Types of Blood Pressure Measurements

It is presently not known if and how a person’s resting BP is influenced by occupational lifting activities. It is therefore of interest to also regard potential effects of occupational lifting on mean arterial pressure, DBP, and pulse pressure. For this reason, we will repeat the linear regression analyses described above on each of these outcomes. Furthermore, a prospective analysis will be applied where the outcome will be classified as a DBP case, similar to the analysis aforementioned relating occupational lifting to the risk of becoming an SBP case. The DBP case will be defined by the shift from no use of antihypertensive drugs in examination n to use of antihypertensive drugs in examination n+1 or an above median delta value of DBP (DBP in examination n+1−DBP in examination n).

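### The only formula for mean arterial pressure is misprinted and, if coded literally, gives values above systolic pressure; mid BP is named as a secondary outcome but left out of the list of regressions (minor)

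*Protocol article*

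**What the plan says.** In the protocol article, Assessment of Outcome sets the primary outcomes and then adds that "secondary analyses will be conducted with pulse pressure", mean arterial pressure and mid BP as outcomes, with a formula for each. The formula for mean arterial pressure is "mean arterial pressure=([2 × DBP] + SBP/3", and one closing bracket follows it. The next formula in the same sentence is "mid BP (½ SBP + ½ DBP", also followed by a closing bracket. Mean arterial pressure is not defined anywhere else.

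Analysis on Other Types of Blood Pressure Measurements expresses interest in "potential effects of occupational lifting on mean arterial pressure, DBP, and pulse pressure" and states that "we will repeat the linear regression analyses described above on each of these outcomes". Those regressions are the ones set out for SBP: cross-sectional and prospective, fitted by generalized estimating equations, and reported as a mm Hg difference with a 95% CI.

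Criteria for Statistical Significance gives the standing of these analyses: "Secondary analyses will be regarded as exploratory and will therefore not be tested for statistical significance". It adds that they may bear on how the primary findings are interpreted.

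**The concern.** The formula is a derivation rule for a planned outcome, and it is the only such rule in the article. By ordinary operator precedence the division by 3 applies to SBP alone. The result is not a mean pressure, because a mean over the cardiac cycle has to lie between the diastolic and the systolic value.

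If the string were programmed as printed, the mm Hg difference attributed to lifting would be on the wrong scale. It would also carry the wrong balance of diastolic and systolic effects, so the error could not be removed afterwards by dividing by a constant. That balance is part of what these analyses are meant to explore, since the article says it is not known whether or how lifting affects resting pressure.

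A smaller point concerns the outcome lists. Mid BP is named and defined in Assessment of Outcome, but the section that assigns the regressions lists only "mean arterial pressure, DBP, and pulse pressure". The article therefore does not say how mid BP will be analysed.

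**Working it through.** **Inputs.** The printed formula and the mid BP formula come from Assessment of Outcome. The cut-point 140/90 is the protocol's own definition of hypertension. The reading 120/80 and the effect of +2 mm Hg SBP with +1 mm Hg DBP are illustrations and are not in the article. The article gives no numerical value of mean arterial pressure, so there is no stated figure to reproduce.

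**Step 1: brackets.** Within the parenthesis that defines mean arterial pressure, two round brackets open and one closes. Two repairs balance the string:
- closing at the end gives 2 × DBP + SBP/3 (the literal form);
- closing after SBP gives (2 × DBP + SBP)/3 (the grouped form).

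**Step 2: values.**

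| Reading | Literal: 2 × DBP + SBP/3 | Grouped: (2 × DBP + SBP)/3 | Mid BP: (SBP + DBP)/2 |
|---|---|---|---|
| 120/80 | 160 + 40 = 200.0 | 280/3 = 93.3 | 100.0 |
| 140/90 | 180 + 46.7 = 226.7 | 320/3 = 106.7 | 115.0 |

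The literal form exceeds SBP whenever 2 × DBP + SBP/3 > SBP, that is, whenever DBP > SBP/3. Essentially every real reading meets that condition. The grouped form and mid BP both lie between DBP and SBP.

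**Step 3: weights.**
- Literal: DBP 2, SBP 1/3. The sum is 2.33, the ratio is 2 ÷ (1/3) = 6:1, and the DBP share is 2/2.33 = 86%.
- Grouped: DBP 2/3, SBP 1/3. The sum is 1, the ratio is 2:1, and the DBP share is 67%.

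Of the two repairs, only the grouped form is a weighted average, as mid BP is.

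**Step 4: consequence for a regression difference.** Both forms are linear in SBP and DBP, so a difference between exposure groups, or a change between examinations, carries the same weights.
- Literal difference: 2 × ΔDBP + ΔSBP/3.
- Grouped difference: (2 × ΔDBP + ΔSBP)/3.
- Literal minus grouped: 2 × ΔDBP − (2/3) × ΔDBP = (4/3) × ΔDBP.

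The error depends only on the DBP effect. A pure DBP effect is multiplied by 2 ÷ (2/3) = 3. A pure SBP effect is unchanged. For ΔSBP = 2 and ΔDBP = 1, the literal form gives 2 + 0.67 = 2.67 and the grouped form gives 4/3 = 1.33, a factor of 2.

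**Step 5: outcome lists side by side.**
- Assessment of Outcome: pulse pressure, mean arterial pressure, mid BP.
- Analysis on Other Types of Blood Pressure Measurements: mean arterial pressure, DBP, pulse pressure, and in addition a DBP-case analysis.

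Mid BP is in the first list and not in the second. DBP is in the second and not in the first.

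**The case against.** The strongest reply is that the string is visibly broken, so it does not settle on the literal form. The opening bracket before the DBP term has little purpose unless it groups the sum to be divided by 3, which points to a bracket that was dropped or shifted. A shift when the text was extracted from the PDF cannot be excluded either. An analyst deriving a familiar quantity would probably use the grouped form, and a mean of 200 mm Hg at 120/80 would stand out in the first descriptive table. Most of this stands. What remains is that the imbalance alone does not fix the reading, since both repairs balance, and the article has no second definition to settle it.

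Four stronger readings are tempting, and the article does not support them.
- *The outcome will be computed wrongly.* This follows only if the misprint is coded literally and goes unchecked.
- *The lifting effect will be inflated.* This is not general: a pure SBP effect is unchanged, and the factor of 2 rests on an assumed +2/+1 mm Hg effect.
- *The main conclusions are at risk.* The hypertension outcome, the SBP case, the DBP case and the power calculation do not use mean arterial pressure, and the secondary analyses are declared exploratory and untested. They may colour the interpretation of the primary findings, but they decide no hypothesis.
- *The two outcome lists contradict each other throughout.* The list in Assessment of Outcome is not exhaustive: it also leaves out the linear SBP analysis, which is planned as secondary. The later appearance of DBP is therefore an addition. Only mid BP, named as an outcome and then not assigned a regression, is a real loose end.

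**Conclusion.** The point holds as a minor correction. The sole definition of mean arterial pressure is misprinted. Taken literally, it yields 200 mm Hg at 120/80 and 226.7 at 140/90, with DBP weighted 6:1 against SBP instead of 2:1. Regressions coded that way would be off by 4/3 of whatever DBP effect exists.

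The weights and the 4/3 excess are exact and need no assumption about the data. The 120/80 reading and the +2/+1 mm Hg effect are illustrations only. That the grouped form is the intended one is an inference from the stray bracket and from the requirement that a mean pressure lie between DBP and SBP. The reach is confined to one exploratory outcome. The omission of mid BP from the regressions is a separate small inconsistency with no numerical consequence that can be shown from the article.

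**What to change.** In Assessment of Outcome, define mean arterial pressure as (2 × DBP + SBP)/3, with brackets that balance. Then settle mid BP: either add it to the outcomes regressed under Analysis on Other Types of Blood Pressure Measurements, or remove it from Assessment of Outcome. Naming DBP in the earlier list as well would be tidy but is not required.

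The cost is one corrected formula and one aligned list. No new data, change of design or change to the primary analyses is involved.

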### Assessment of Covariates

Previously a number of factors have been shown to be associated both with occupational workload and BP. Thus, those factors will be included as covariates: sex (male or female) [14,15]; age (categories of <40, 50-59, 60-69, 70-79, and >80 years) [16]; body mass index (BMI; categories of <18.5, 18.5-24.9, 25.0-29.9, and ≥30kg/m^2^) [17,18] calculated from objectively measured body height and weight; smoking (categories of nonsmoking and currently smoking) [19,20]; length of education (categories of uneducated, low educated up to 3 years, vocationally educated 1-3 years, higher educated, and academically educated) [1,21]; for the prospective analysis only, additional adjustment for vital exhaustion, split in 4 categories defined elsewhere (0, 1-4, 5-9, and 10-17) [22,23]; self-rated cardiorespiratory fitness (categories of lower, similar, and higher cardiorespiratory fitness compared with peers of same sex and age) [24]; SBP at baseline (categories of 80-89, 90-99, 100-109, 110-119, 120-129, 130-139, and ≥140 mm Hg) [13]; and DBP at baseline (categories of 40-49, 50-59, 60-69, 70-79, 80-89, and ≥90 mm Hg).

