### Primary Statistical Analyses

Logistic regression will be used to estimate the odds of becoming a case from examination n to n+1 as a function of heavy occupational lifting. For the cross-sectional analysis, there will be a possibility of 3 observations per participant, 1 from each examination. For the prospective analysis, there will be a possibility of 2 observations per participant, 1 from the third to the fourth examination and one from the fourth to the fifth examination. The cross-sectional analysis will be controlled for sex, age, BMI, smoking, and education. The prospective analysis will, in addition to the variables of the cross-sectional analysis, be controlled for self-rated cardiorespiratory fitness, vital exhaustion, and BP at baseline. Self-rated cardiorespiratory fitness and vital exhaustion will only be included as covariates in the prospective analysis where the main point of interest is new cases and not prevalent cases as in the cross-sectional analysis. Generalized estimating equations will be used to estimate the parameters. Observations from the same person will be treated as repeated measurements. A first order autoregressive correlation structure is assumed. Should the estimated covariance matrix fail to converge, then we will resort to a variance component correlation structure.

The significance test will be based on the empirical SE and the Wald Statistic. The odds ratio (OR) between the exposed and the nonexposed will be calculated and presented with a 95% CI. The CI will be based on the empiric SE.

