### Differences in the Study Population

Smaller numerical differences were observed between the participants answering on the level of OPA and the attending participants.

Cross-sectionally, the participants responding to the level of OPA were 9.8 years younger (mean age 49.0 years among the participants answering on the level of OPA and 58.8 years among the attending), had a higher level of education than the attending participants (13.87% [1619/11,670] participants responding to the level of OPA were noneducated and 20.69% [4328/20,922] among the attending), and a higher proportion of the participants responding to the level of OPA stated to be exposed to heavy occupational lifting (14.04% [1638/11,670] among the participants responding to the level of OPA and 8.48% [1774/20,922] among the attending participants).

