**Figure 3 figure3:**
[figure not shown]
Flow of the observations and participants in the third, fourth, and fifth examinations of the Copenhagen City Heart Study. OPA: occupational physical activity; obs: observation.

**Table 7 table7:** Baseline characteristics of the participants responding to the level of occupational physical activity for the cross-sectional analysis; 11,670 observations on 7166 participants.

Cross-sectional analysis		Mean (SD)	n (%)	Range
Age (years)		49.0 (13.8)		20.3-99.7
Sex (% female)			5330 (54.3)	
Body mass index (kg/m^2^)		25.2 (4.3)		12.8-56.6
Smoking (% current smokers)			4292 (36.9)	

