These nonsignificant differences between the attending participants and participants responding to the level of OPA in the cross-sectional and prospective populations may affect the prevalence of hypertension. The younger age of the participants responding to the level of OPA as well as their higher proportion of being educated might lower the prevalence of hypertension among these participants compared with those attending [28]. Conversely, may those participants responding to the level of OPA have a higher prevalence of hypertension due to their higher exposure to heavy occupational lifting than among the attending participants. In the prospective population, the small difference in proportion of participants stating to have a level of cardiorespiratory fitness similar to their peers, is not believed to affect the prevalence of hypertension, as the proportion of participants stating to have a higher level of cardiorespiratory fitness than their peers is similar among those participants responding to the level of OPA and those attending.

**Table 8 table8:** Baseline characteristics of the participants responding to the level of occupational physical activity for the prospective analysis; 5932 observations on 4089 participants.

Prospective analysis		Mean (SD)	n (%)	Range
Age (years)		48.0 (11.8)		20.3-84.3
Sex (% female)			3301 (55.7)	
BMI (kg/m^2^)		25.0 (4.0)		16.0-52.5
Smoking (% current smokers)			2311 (39.1)	

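### The age coding used in both primary models has no category for ages 40-49, the decade that contains both mean ages

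*Protocol article*

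**What the plan says.** Methods, Assessment of Covariates, lists age as "age (categories of <40, 50-59, 60-69, 70-79, and >80 years". The bands go from under 40 straight to 50-59, and the top band starts above 80.

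Primary Statistical Analyses puts this covariate in both primary models. For the first: "The cross-sectional analysis will be controlled for sex, age, BMI, smoking, and education". The prospective model will, "in addition to the variables of the cross-sectional analysis, be controlled for self-rated cardiorespiratory fitness, vital exhaustion, and BP at baseline", so it takes over the same age variable.

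Stratification by Age splits the prospective sample at 50 years and keeps the covariates of the primary prospective analysis.

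On where ages lie, Differences in the Study Population gives "mean age 49.0 years among the participants answering on the level of OPA", and 48.0 years for the prospective responders. Table 7 ("11,670 observations on 7166 participants") reports mean 49.0, SD 13.8, range 20.3-99.7. Table 8 ("5932 observations on 4089 participants") reports mean 48.0, SD 11.8, range 20.3-84.3. No section gives counts by age band.

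**The concern.** A model can use an observation only if each covariate has a value. Under the stated coding, a participant aged 40 to 49 has no age category. An analyst who programs the list as written gets a missing value for that decade and loses those records. An analyst who notices must choose between a new 40-49 band, a lowest band widened to under 50, and a 40-59 band. These choices adjust for age differently, and the article itself says its covariates were chosen because they are linked to both workload and blood pressure.

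This is more than detail left to a fuller plan, because the categories are stated and they are incomplete. Timing also matters. Flow of Participants says the blood pressure and drug-use data come after the article's submission. A coding settled before then is prespecified. One settled later is chosen with the outcomes in hand.

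**Working it through.** **Inputs.** Age mean and SD: 49.0 and 13.8 (Table 7, 11,670 observations); 48.0 and 11.8 (Table 8, 5932 observations). Ages are read in completed years, so the missing band is 40 to under 50. The article states no share by age band, so there is no figure of its own to reproduce. The distribution shape is an assumption.

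**Share in the gap, normal approximation.** Share = Φ((50 − mean)/SD) − Φ((40 − mean)/SD).

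- Cross-sectional: Φ(1.0/13.8) − Φ(−9.0/13.8) = 0.529 − 0.257 = 0.272. Times 11,670, this is about 3170 observations.
- Prospective (Table 8): Φ(2.0/11.8) − Φ(−8.0/11.8) = 0.567 − 0.249 = 0.318. Times 5932, this is about 1890 observations.

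**Other shapes, same mean and SD.**

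| Assumed shape | Cross-sectional | Prospective |
|---|---|---|
| Normal | 27.2% | 31.8% |
| Normal truncated to the reported range | 26.6% | 31.1% |
| Beta scaled to the reported range | 26.4% | 29.8% |
| Gamma | 29.2% | 33.6% |
| Uniform (extreme case) | 20.9% | 24.5% |

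No shape tried makes the gap small.

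**Age 80.** Reading this as 80 to under 81, the normal approximation gives about 0.2% (25 observations) cross-sectionally and under 0.1% (about 5) prospectively. It is worth correcting in the same edit but has no practical weight.

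**Does the plan allow for a loss?** No. Table 5 expects 11,670 cross-sectional observations, the full Table 7 count. Its 4746 prospective observations match 5932 × 0.80 = 4745.6, which removes only the 20% assumed hypertensive at baseline. Neither figure has a deduction for undefined age.

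**Cost if the records were dropped.** Cross-sectionally, 11,670 × (1 − 0.272) is about 8500 observations. With exposure and case mix unchanged, standard errors grow by 1/√0.728 = 1.17. Prospectively the factor would be 1/√0.682 = 1.21, if the 32% share also held in the analysed set.

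**Cost if the lowest band were read as under 50.** One band covering ages 20 to 49 would hold Φ((50 − mean)/SD), that is about 53% of cross-sectional and 57% of prospective observations, with no age adjustment inside it.

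**Under-50 stratum.** As written, its only defined band is under 40, and 0.318/0.567, about 56% of the stratum, has no category. With a band of under 50 there is again a single band. On either reading, age is not adjusted for within the stratum that Stratification by Age calls possibly the more relevant one.

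**The case against.** The strongest reply is that this is a typing slip that nobody would follow. The other bands run by decade, and the rest of the article shows that people in their forties are meant to be analysed: Inclusion Criteria has no age limit, Table 5 expects no loss, and the stratified analysis speaks of everyone under 50. An analyst would soon notice a quarter or more of the records without an age value. This stands as far as it goes, and a reader should not infer that these observations will in fact be lost. It does not settle whether 40-49 was left out or <40 was written for <50, and those are different models.

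Several stronger readings are tempting and not supported:

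- **A count for the analysed prospective set.** Applying 32% to the 4746 in Table 5 gives about 1510. But 32% comes from the 5932 responders in Table 8. The 4746 are the expected normotensive subset, whose age distribution is not given and may differ.
- **A known bias in the odds ratios.** Wide age bands can leave residual confounding, but the article gives no age distribution by lifting status, so no size can be derived. Nor does it rank age above the other covariates.
- **A fault in the baseline blood pressure bands.** The prospective model lists "SBP at baseline (categories of 80-89, 90-99, 100-109, 110-119, 120-129, 130-139, and ≥140 mm Hg", while entry requires "that he or she was normotensive at examination n", so the ≥140 band, and likewise diastolic ≥90, should be empty. An empty band adds no parameter and no bias. Regression to the mean within 10 mm Hg bands would distort the lifting odds ratio only if lifting were related to baseline pressure inside a band, and nothing in the article shows that.
- **A need for splines.** Pooling ages 20-39 and using decade bands are conventional choices. Continuous terms are a preference beyond the demonstrated error.

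**Conclusion.** The point holds for the 40-49 gap. A stated rule for a covariate in both primary models leaves the central decade of the sample without a category, and nothing elsewhere in the article repairs it. The size is an estimate: about 27% of the 11,670 cross-sectional observations and about 32% of the 5932 prospective responder observations under normality, with 21% to 34% across all shapes tried. It rests on the means and SDs in Tables 7 and 8 and applies to participants who answered the activity question, not to the final analysis sets. The consequence is an undefined coding with several possible repairs. It is not a demonstrated loss of data or a demonstrated bias. It should be corrected because it affects both primary models and leaves the under-50 analysis without a usable age adjustment.

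**What to change.** In Assessment of Covariates, give the age categories as <40, 40-49, 50-59, 60-69, 70-79 and ≥80 years. State that this coding applies in all models, including the age-stratified analysis, where the under-50 stratum then has two bands. Record the correction before the blood pressure and drug-use data are received.

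The cost is one sentence and one extra model parameter, with no change to Table 5. Entering age as a continuous term is optional. Deleting the empty baseline bands (systolic ≥140, diastolic ≥90) is tidying only.
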